# Ethical issues

This study will not be conducted until ethical clearance is obtained from the Medunsa Research Ethics Committee. Since the sources of research data are participants’ responses to study measures, there are potential risks to human subjects. These include negative consequences if confidentiality of information obtained in the study (including subject identity as a research participant) were compromised; embarrassment, discomfort, or distress in response to the interviews discussing substance use, and frustration in completing assessment measures.

While the risks of administering the behavioral and demographic data questionnaire to the study participants of this study are considered minimal, steps will be taken to reduce this risk further by employing specially trained and supervised research assistants who will know how to prevent or handle any possible negative consequence.

#### Adequacy of Protection against Risks

Informed Consent: Research staff will conduct the informed consent process in a private room located in the area of the clinic. A research staff person will sit with the participant and work through the informed consent form together. After a detailed description of all study goals, requirements and risks are presented to eligible participants; written consent will be obtained prior to their enrolment into the study. Informed consent forms will be given and explained in the preferred language of the participant (English-Annex 7, or seTswana-Annex 8). The consent process is expected to take 10 minutes. Participants can take as long as they wish to decide whether or not to participate.

Voluntariness: All participation in this study will be voluntary. Participants may stop the data collection process at any time for any reason. Refusal to take part in this project will have no bearing on services at the health facility; all individuals, whether they agree to participate or refuse, will continue to receive treatment for their illness based on established standard of care. This will be made clear to the interviewees both before and during the consenting process.

Accountability of researchers: The names of the investigators will be included on all consent forms with phone numbers and addresses for the participants to use if they have any questions.

Data monitoring and protection: The researcher will be responsible for data management. All data forms and records collected during this research will be held in a secure location at the University of Limpopo for the duration of the proposed research. Confidentiality of all respondents will be ensured through the replacement of any personal information with unrelated unique identifiers. Wherever relevant, names and location information will be separated from the electronic data that are processed for analysis. The only identifiers used during the analysis will be a unique identification number.

Potential benefits: Essentially the participants may benefit from an increased awareness of their own alcohol risk behaviors and be empowered to do something about it. They will also learn in the experimental group from the intervention about how to reduce risky drinking.

While the immediate benefits of the survey questionnaire to individuals will be minimal, the information disseminated during this study will assist greatly with alcohol intervention program planning and implementation. The community as a whole will benefit from these data which will assist public health and clinical workers in the targeting of efforts to control alcohol problems in the area. The risk to the study subjects is minimal and reasonable, given the health risks associated with alcohol.

All participants in this study will be persons with medium risk drinking. It is anticipated that participants in the intervention will acquire knowledge and skills, and will receive support needed to reduce their alcohol risks. All participants will receive the intervention. In addition to the direct benefits associated with participation, this research is expected to yield important new information on intervention models for reducing alcohol risk behaviours in South African hospital patients. All field staff will be extensively trained in risk management and human participant protections.

#### Confidentiality

All research data obtained from participants will be labeled with a code number and not the participant’s name. Only the code number will appear on measures, data records, and computer files.

Obtaining Consent

Consent to participate will be obtained in a 2-stage process. Research assistants will initially ask for informed consent to conduct health screening and collect some basic demographic information and check eligibility to take part. No identifiable information will be collected at this stage. Patients who then are positive on the AUDIT (alcohol medium risk score), as applicable, will have the study explained to them verbally by another research assistant counselor and in writing (using the patient information sheet, annex 7-8). Informed consent will be obtained at this second stage which will include permission to give the patient's data and contact details to the research staff, and participate in the intervention and follow up after 3 and 12 months (see Annex 7-8: Consent form).

# Dissemination of research findings:

Results from the outcome evaluation will be disseminated through peer reviewed journal publications, published reports and presentations for dissemination to the university and district departments of health as well as presentations at relevant local meetings and conferences. In terms of feedback for hospital staff a summary sheet of the findings will be prepared and a full report will be made available.

# Time line and research activity

| **Research Activity** | **Month/Year** |
| --- | --- |
| Phase 1: Ethics approval and field preparation  1) Full ethics protocol submission  2) Preparatory visits to health facilities  3) Recruitment and training of research assistants/counselors  4) Pre-test and printing of questionnaires  Phase 2: Recruitment of 552 participants  1) Brief interventions of alcohol problems  2) Project management meetings, teleconferences  3) Interview Quality control  4) Data entry/ analysis and publication    Phase 3: First follow-up interviews with participants (3 months)  1) Interviews  2) Project management meetings  3) Quality control  4) Data entry/ analysis/Publication  Phase 4: Second follow-up interviews with participants (12 months)  1) Interviews  2) Project management meetings  3) Quality control  4) Data entry/ analysis/Publication | July-Aug 2011  Aug 2011  Aug 2011  Aug 2011  Sept-Nov 2011  Sept-Nov 011  Sept-Nov2011  Dec 2011  Dec-Feb 2012  Dec-Feb 2012  Dec- Feb 2012  Feb-Apr 2012  Oct-Dec 2012  Oct- Dec 2012  Oct- Dec 2012  Jan-Feb 2013 |

# Budget

| **Activities** | **Budget (R)** |
| --- | --- |
| Teleconference with research team and consultant in Belgium | R 4,000 |
| Salaries 2 full time field workers # R 6000 pm x 6 months | R 72,000 |
| Top up pharmacy assistant adherence measurement | R 5,000 |
| Training the field workers | R 2,000 |
| Pre-testing questionnaires | R 1,000 |
| Printing questionnaires, inform consent, reports | R 6,000 |
| Data/ interview quality control | R 3,000 |
| Recruitment and first interview (drink) R 6 per case x 552 | R 3,312 |
| 1^st^ and 2^nd^ follow up ( R 12 x 552) | R 6,624 |
| Telephone for follow up | R 4,000 |
| Data entry ( R 10 X 552 X 4) | R 22,080 |
| Publication fee and editing (expected 5 papers) | R 30,000 |
| **Total** | **R 159,016** |

# Annexes

#### Annex 1: Patient interview schedule and Demographic Characteristics

Interviewer: _______________________________

Place of Interview:__________________________

Start Time of Interview:_______________________

End Time of Interview:_______________________

P.I.D.______________________________________

**CONFIDENTIAL**

| **Patient Interview Schedule** | | |
| --- | --- | --- |
| Interview type | [ ] 1. Baseline Visit  [ ] 2. 1st Follow-up (3 months)  [ ] 3. 2nd Follow-up (12 months) | |
| Current physical address of participant:  ____________________________________________________________________________________________ | Name of village/suburb:_____________________________________  _____________________________________________________  Name of neighbour: ________________________________________  ______________________________________________  Nearest shop, church, school (name):__________________________  _____________________________________________________ | |
| Possible new physical address within a one year, if yes, detail as above: | _______________________________________________________________________________________________________________________________________________________________ | |
| Health facility name: | _____________________________________________________ | |
|  |  |  |
| Result codes  [ ] 1. Completed  [ ] 2. Respondent not available  [ ] 3. Respondent refused  [ ] 4. Partially completed  [ ] 5. Other (specify)_________________________________________________________________ | |  |

| **Part 1. Socio-demographic data-English** | | | | |
| --- | --- | --- | --- | --- |
| 1.1 How would you describe yourself in terms of population group? | [ ] 1. Black African  [ ] 2. Coloured | [ ] 3. Indian or Asian  [ ] 4. White | | [ ] 5. Other (specify) |
| 1.2 What language do you speak most often in your household? | [ ] 1. Afrikaans  [ ] 2. English  [ ] 3. IsiNdebele  [ ] 4. Isiswati  [ ] 5. IsiXhosa | [ ] 6. IsiZulu  [ ] 7. Sesotho sa borwa  [ ] 8. Sepedi  [ ] 9. Setswana  [ ] 10. Tshivenda | | [ ] 11. Xitsonga  [ ] 12. Other African  [ ] 13. Other European  [ ] 14. Indian language  [ ] 15. Other (specify) |
| 1.3 Age in completed years | ................................. | | | |
| 1.4 Gender | [ ] 1. Male | [ ] 2. Female | | |
| 1.5 What is your current marital status? | [ ] 1. Never married  [ ] 2. Currently married  [ ] 3. Separated | [ ] 4. Divorced  [ ] 5. Widowed  [ ] 6. Living together like married partners (cohabiting) | | |
| 1.6 What is your highest educational qualification? TICK ONE ANSWER ONLY | [ ] 1. No schooling  [ ] 2. Primary education (Grade 1-6)  [ ] 3. Secondar educatuion (Grade 7-12) | | [ ] 4. Diploma(s) / Occupational certificate(s)  [ ] 5. First degree(s)/ Higher diploma(s)  [ ] 6. Honours / Master’s degree(s) and higher | |
| 1.7 What is the main source of your household income? | [ ] 1. Formal salary/earnings on which you pay income tax  [ ] 2. Contributions by adult family members or relatives  [ ] 3. Contributions by younger family members or relatives (<18 years)  [ ] 4. Government pensions/grants (e.g. old age pension, disability grant)  [ ] 5. Grants/donations by private welfare organizations  [ ] 6. Other (specify)___________________________________________________________  [ ] 7. No income (other than social grant)____________________________________________ | | | |
| 1.8 What is the type of neighbourhood where you live? | [ ] 1. Rural village  [ ] 2. Informal settlements  [ ] 3. Urban/Town/metropolitan area  [ ] 4. Township  [ ] 5. Farm | | | |

#### Annex 2: Health-related quality of life (QoL)

###### Quality of life

| **Health-related quality of life** | | | | | | | | | | | | |
| --- | --- | --- | --- | --- | --- | --- | --- | --- | --- | --- | --- | --- |
| 1. How would you rate your quality of life? | [ ] 1. Very poor | [ ] 2. Poor | | | [ ] 3. Neither poor nor good | | [ ] 4. Good | | | [ ] 5. Very good | | |
| 2 How satisfied are you with your health? | [ ] 1. Very dissatisfied | [ ] 2. Dissatisfied | | | [ ] 3. Neither satisfied nor dissatisfied | | [ ] 4. Satisfied | | | [ ] 5. Very satisfied | | |
| The following questions ask about **how much** you have experienced certain things in the last two weeks. | | | | | | | | | | | | |
|  | | | **Not at all** | **A little** | | **A moderate amount** | | | **Very much** | | | **An extreme amount** |
| 3 To what extent does physical pain prevent you from doing what you need to do? | | | [ ] 1. | [ ] 2. | | [ ] 3. | | | [ ] 4. | | | [ ] 5. |
| 4 How much are you bothered by physical problems related to HIV/AIDS? | | | [ ] 1. | [ ] 2. | | [ ] 3. | | | [ ] 4. | | | [ ] 5. |
| 5 How much do you need any medical treatment to function in your daily life? | | | [ ] 1. | [ ] 2. | | [ ] 3. | | | [ ] 4. | | | [ ] 5. |
| 6 How much do you enjoy life? | | | [ ] 1. | [ ] 2. | | [ ] 3. | | | [ ] 4. | | | [ ] 5. |
| 7 To what extent do you feel your life to be meaningful? | | | [ ] 1. | [ ] 2. | | [ ] 3. | | | [ ] 4. | | | [ ] 5. |
| 8 To what extent are you bothered by people blaming you for having HIV/AIDS? | | | [ ] 1. | [ ] 2. | | [ ] 3. | | | [ ] 4. | | | [ ] 5. |
| 9 How much do you fear for the future because of HIV/AIDS? | | | [ ] 1. | [ ] 2. | | [ ] 3. | | | [ ] 4. | | | [ ] 5. |
| 10 How much do you worry about death because of HIV/AIDS? | | | [ ] 1. | [ ] 2. | | [ ] 3. | | | [ ] 4. | | | [ ] 5. |
| 11 How well are you able to concentrate? | | | [ ] 1. | [ ] 2. | | [ ] 3. | | | [ ] 4. | | | [ ] 5. |
| 12 How safe do you feel in your daily life? | | | [ ] 1. | [ ] 2. | | [ ] 3. | | | [ ] 4. | | | [ ] 5. |
| 13 How healthy is your physical environment? | | | [ ] 1. | [ ] 2. | | [ ] 3. | | | [ ] 4. | | | [ ] 5. |
|  | | | **Not at all** | **A little** | | **Moderately** | | | **Mostly** | | | **Completely** |
| 14 Do you have enough energy for everyday life? | | | [ ] 1. | [ ] 2. | | [ ] 3. | | | [ ] 4. | | | [ ] 5. |
| 15 Are you able to accept your bodily appearance? | | | [ ] 1. | [ ] 2. | | [ ] 3. | | | [ ] 4. | | | [ ] 5. |
| 16 Have you got enough money to meet your needs? | | | [ ] 1. | [ ] 2. | | [ ] 3. | | | [ ] 4. | | | [ ] 5. |
| 17 To what extent do you feel accepted by the people you know, whether or not they are aware of your HIV/AIDS? | | | [ ] 1. | [ ] 2. | | [ ] 3. | | | [ ] 4. | | | [ ] 5. |
| 18 How available to you is the information that you need in your day-to-day life? | | | [ ] 1. | [ ] 2. | | [ ] 3. | | | [ ] 4. | | | [ ] 5. |
| 19 To what extent do you have the opportunity for leisure activities? | | | [ ] 1. | [ ] 2. | | [ ] 3. | | | [ ] 4. | | | [ ] 5. |
| 20 How well are you able to get around? | | | [ ] 1. | [ ] 2. | | [ ] 3. | | | [ ] 4. | | | [ ] 5. |
|  | | | **Very dissatisfied** | **Dissatisfied** | | **Neither satisfied nor dissatisfied** | | | **Satisfied** | | | **Very satisfied** |
| 21 How satisfied are you with your sleep? | | | [ ] 1. | [ ] 2. | | [ ] 3. | | | [ ] 4. | | | [ ] 5. |
| 22 How satisfied are you with your ability to perform your daily activities? | | | [ ] 1. | [ ] 2. | | [ ] 3. | | | [ ] 4. | | | [ ] 5. |
| 23 How satisfied are you with your capacity to work? | | | [ ] 1. | [ ] 2. | | [ ] 3. | | | [ ] 4. | | | [ ] 5. |
| 24 How satisfied are you with yourself? | | | [ ] 1. | [ ] 2. | | [ ] 3. | | | [ ] 4. | | | [ ] 5. |
| 25 How satisfied are you with your personal relationships? | | | [ ] 1. | [ ] 2. | | [ ] 3. | | | [ ] 4. | | | [ ] 5. |
| 26 How satisfied are you with your sex life? | | | [ ] 1. | [ ] 2. | | [ ] 3. | | | [ ] 4. | | | [ ] 5. |
| 27 How satisfied are you with the support you get from your friends? | | | [ ] 1. | [ ] 2. | | [ ] 3. | | | [ ] 4. | | | [ ] 5. |
| 28 How satisfied are you with the condition of your living space? | | | [ ] 1. | [ ] 2. | | [ ] 3. | | | [ ] 4. | | | [ ] 5. |
| 29 How satisfied are you with your access to health services? | | | [ ] 1. | [ ] 2. | | [ ] 3. | | | [ ] 4. | | | [ ] 5. |
| 30 How satisfied are you with your transport? | | | [ ] 1. | [ ] 2. | | [ ] 3. | | | [ ] 4. | | | [ ] 5. |
| **The following question refers to how often you have felt or experienced certain things in the last two weeks.** | | | | | | | | | | | | |
| 31 How often do you have negative feelings such as depressed mood, despair, anxiety? | [ ] 1. Never | [ ] 2. Seldom | | | [ ] 3. Quite often | | | [ ] 4.Very often | | | [ ] 5. Never | |

###### Depression:

| **CES-D** | | | | |
| --- | --- | --- | --- | --- |
| **For each of these statements, please indicate how often you felt this way during the past week** | | | | |
|  | Rarely (<1day) | Some/little (1-2 days) | Much  (3-4 days) | Most  (5-7 days) |
| 1. I was bothered by things that usually don’t bother me | 1 | 2 | 3 | 4 |
| 2. I had trouble keeping my mind on what I was doing | 1 | 2 | 3 | 4 |
| 3. I felt that everything I did was an effort | 1 | 2 | 3 | 4 |
| 4. I felt depressed | 1 | 2 | 3 | 4 |
| 5. I felt hopeful about the future | 1 | 2 | 3 | 4 |
| 6. I felt fearful | 1 | 2 | 3 | 4 |
| 7. My sleep was restless | 1 | 2 | 3 | 4 |
| 8. I was happy | 1 | 2 | 3 | 4 |
| 9. I felt lonely | 1 | 2 | 3 | 4 |
| 10. I could not get going | 1 | 2 | 3 | 4 |

###### Sexual Behaviour

| **Sexual behaviour** | | | | | | |
| --- | --- | --- | --- | --- | --- | --- |
| **Please think carefully about the past 3-months and mark your answers**. | | | | | | |
| 1. Have you had sexual intercourse in the past 3 months | Yes [ ] | No [ ] | If no, go to next question | | | |
| 1. How many men have you had sex with in the past 3 months? | 0 | 1 | 2 | 3 | 4 | 5 or more men |
| 1. How many women have you had sex with in the past 3 months? | 0 | 1 | 2 | 3 | 4 | 5 or more men |

Now please think carefully about the past 3 months.

**In the past 3 months –How many times did you……**

| 1. Have sex **without** condoms (protection)? | 0 | 1-2 | 3-5 | 6-10 | 11-20 | 21-30 | 31-40 | 41 or more times |
| --- | --- | --- | --- | --- | --- | --- | --- | --- |
| 1. Have sex **with** use of condoms (protection)? | 0 | 1-2 | 3-5 | 6-10 | 11-20 | 21-30 | 31-40 | 41 or more times |
| 1. Drank alcohol before sex? | 0 | 1-2 | 3-5 | 6-10 | 11-20 | 21-30 | 31-40 | 41 or more times |
| 1. Your sex partner drank alcohol before sex? | 0 | 1-2 | 3-5 | 6-10 | 11-20 | 21-30 | 31-40 | 41 or more times |
| 1. Use drugs (Dagga, mandrax, or others) before sex? | 0 | 1-2 | 3-5 | 6-10 | 11-20 | 21-30 | 31-40 | 41 or more times |
| 1. Your sex partner used drugs (Dagga, mandrax, or others) before sex? | 0 | 1-2 | 3-5 | 6-10 | 11-20 | 21-30 | 31-40 | 41 or more times |

| 1. Use a condom at last sex, with partner whom unknown or negative HIV status | [ ] 1. Yes [ ] 2. No |
| --- | --- |
| 1. **In the past 3 months –I have** Disclosed my HIV status to my last sex partner | [ ] 1. Yes [ ] 2. No |

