#### Objectives:

- - 1. To measure the prevalence of alcohol consumption among HIV positive hospital outpatients;
    2. To describe drinking patterns, health status, quality of life and sexual behavior among HIV positive out-patients, and identify medium risk drinkers needing intervention;
    3. To compare level of alcohol consumption, health status, quality of life, level of adherence to ART and sexual behavior among medium risk drinkers within the previously identified group between pre intervention, 3 months and 12 months after intervention;
    4. To compare **levels of** (a) alcohol consumption, (b) adherence level to ART, (c) quality of life, (d) health status and (e) number of patients with virological and immunological failure, between intervention and control group at 3 and 12 months;
    5. To compare **changes in** (a) alcohol consumption, (b) adherence level to ART, (c) quality of life, (d) health status and (e) number of patients with virological and immunological failure, between intervention and control group at 3 and 12 months.

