###### Sexual behavior

To study the sexual behavior of HIV patients who consume moderate amounts of alcohol before and after intervention, we included a questionnaire with questions on sexual behavior. This questionnaire will be administered at baseline and every follow up visit.

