###### Sexual Behaviour-Setswana

| **Sexual behaviour** | | | | | | |
| --- | --- | --- | --- | --- | --- | --- |
| Nagana sentle ka ga dikgwedi tse 3 tse di fitileng mme o tlhophe karabo ya gago. | | | | | | |
| 1. O ne wa tsena mo thobalanong mo kgweding tse tharo tse di fitileng? | Ee [ ] | Nya [ ] | Ga o re nya, e ya ko potso ya bolesome | | | |
| 2. O robalane le borre ba le bakae mo kgweding tse tharo tse di fitileng? | 0 | 1 | 2 | 3 | 4 | 5 kgotsa ba go feta |
| 3. O robalane le bomme ba le bakae mo kgweding tse tharo tse di fitileng? | 0 | 1 | 2 | 3 | 4 | 5 kgotsa ba go feta |

Jaanong nagana sentle ka ga dikgwedi tse 3 tse di fitileng.

Mo kgweding tse 3 tse di fitileng-Ke makgetho a le makae……

| 4. O tsene mo thobalanong ka ntle le go dirisa kgotlhopo? | 0 | 1-2 | 3-5 | 6-10 | 11-20 | 21-30 | 31-40 | 41 kgotsa ba go feta |
| --- | --- | --- | --- | --- | --- | --- | --- | --- |
| 5. O tsene mo thobalanong o dirisa kgotlhopo? | 0 | 1-2 | 3-5 | 6-10 | 11-20 | 21-30 | 31-40 | 41 kgotsa ba go feta |
| 6. O tsene mo thobalanong o nwele bojalwa? | 0 | 1-2 | 3-5 | 6-10 | 11-20 | 21-30 | 31-40 | 41 kgotsa ba go feta |
| 7. Molekane wa gago a nwele bojalwa pele le robalana? | 0 | 1-2 | 3-5 | 6-10 | 11-20 | 21-30 | 31-40 | 41 kgotsa ba go feta |
| 8. O dirisitse diritibatsi pele ga thobalano? | 0 | 1-2 | 3-5 | 6-10 | 11-20 | 21-30 | 31-40 | 41 kgotsa ba go feta |
| 9. Molekane wa gago a dirisitse diritibatsi pele ga thobalano? | 0 | 1-2 | 3-5 | 6-10 | 11-20 | 21-30 | 31-40 | 41 kgotsa ba go feta |

| 10. O ne wa se dirise kgolhopo le molekane yo o sa itseng maemo a gagwe a HIV | [ ] 1. Ee [ ] 2. Nya |
| --- | --- |
| **11. Mo kgweding tse 3 tse di fitileng –Ke itsisitse** Molekane wa bofelo o ke neng ka tsena mo thobalanong le ena ka maemo a me a HIV | [ ] 1. Ee [ ] 2. Nya |

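### The disclosure item cannot tell earlier disclosure from none, and the condom item has no not-applicable option and appears to run in opposite directions in English and Setswana

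*Protocol*

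**What the plan says.** The items are in the protocol, Annex 2, Sexual Behaviour, and its Setswana counterpart. Only the Setswana form prints the numbers 1 to 11; counting in order, the English items correspond.

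- **Item 11, English.** Under a lead-in limiting it to the past three months, the patient states whether he or she has "Disclosed my HIV status to my last sex partner". The boxes are Yes and No.
- **Item 10, English.** "Use a condom at last sex, with partner whom unknown or negative HIV status", again with Yes and No only.
- **Item 10, Setswana.** "O ne wa se dirise kgolhopo le molekane yo o sa itseng maemo a gagwe a HIV". On my reading this asks whether a condom was *not* used with a partner of unknown HIV status. A Setswana speaker should confirm it.
- **Skip after item 1 (any intercourse in the past three months), English.** "If no, go to next question".
- **Same skip, Setswana.** "Ga o re nya, e ya ko potso ya bolesome", which sends a No to question ten.

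On timing, the Sexual behavior section states: "This questionnaire will be administered at baseline and every follow up visit". Follow-up is at 3 and 12 months. Objective 2 describes sexual behaviour, and objective 3 compares "level of adherence to ART and sexual behavior among medium risk drinkers" before the intervention and at 3 and 12 months. Objectives 4 and 5, which compare the arms, do not list it. The Alcohol consumption section says questionnaires are given in English or Tswana.

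**The concern.** Telling a given partner is normally a single event, and what matters afterwards is that the partner knows. An item that credits only disclosure inside a moving three-month window measures recent events. It does not measure the state one would want to follow over a year.

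The condom item is conditional on a type of partner that some patients will not have, and the form gives them nowhere to say so. If its direction also changes with language, pooled answers have no single meaning.

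At stake is whether these two items can support the description and the change over time in objectives 2 and 3. This is a fault in what is collected. An analysis plan cannot supply information that was never asked for.

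**Working it through.** The protocol states no rate, scoring rule or denominator for either item, so there is no figure of its own to reproduce. The check is a reading of the items, followed by illustrations on assumed values.

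**1. Disclosure over the visits (item 11).** The partner continues throughout and visits are at months 0, 3 and 12. The literal answer is Yes only if disclosure fell in the three months before the visit.

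| Time of disclosure | Month 0 | Month 3 | Month 12 |
| --- | --- | --- | --- |
| Years before baseline | No | No | No |
| 1 month before baseline | Yes | No (4 months ago) | No (13 months ago) |
| Month 5 | No | No | No (7 months ago) |
| Never | No | No | No |

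Rows 1, 3 and 4 look identical although the partner knows in two of them. Row 2 shows a fall with no change in behaviour. The windows cover months −3 to 0, 0 to 3 and 9 to 12, so disclosure between months 3 and 9 is never recorded.

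*Size, on assumed values.* Recorded Yes = p × (1 − f), where p is the share whose last partner has been told and f is the share of those told before the window.

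- Lowest: p = 0.50, f = 0.90 gives 0.50 × 0.10 = 0.05.
- Highest: p = 0.70, f = 0.30 gives 0.70 × 0.70 = 0.49.

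True disclosure of 50–70% would thus appear as 5–49%.

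**2. Who reaches items 10 and 11 without a fitting answer.** In English, a No at item 1 leads to item 2, so nothing is skipped. In Setswana it leads past items 2 to 9 to item 10, the condom item. Neither route takes a patient without recent sex past items 10 and 11. If 10–30% of the 552 patients had no sex in the window (assumption), that is 0.10 × 552 ≈ 55 to 0.30 × 552 ≈ 166 patients.

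**3. Meaning of a tick at item 10, by language.**

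| Situation | English | Setswana (as I read it) |
| --- | --- | --- |
| Condom used, partner of unknown status | Yes | No |
| Condom not used, partner of unknown status | No | Yes |
| Partner known to be HIV negative | Covered | Not covered |
| No sex, or only an HIV-positive partner | No fitting box; a No looks like unprotected sex | No fitting box; a No looks like no risk |

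*Illustration, all values assumed.* Let 30% have no applicable partner and tick No. Among the other 70%, let 20% have had unprotected sex, and take the partner definition as the same in both languages.

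- Unprotected: 0.70 × 0.20 = 0.14. Protected: 0.70 × 0.80 = 0.56.
- English: No = 0.14 + 0.30 = 0.44.
- Setswana: Yes = 0.14; No = 0.56 + 0.30 = 0.86.

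The same population gives 44% No on one form and 86% No on the other. With 10% not applicable, English No is 0.90 × 0.20 + 0.10 = 0.28, and Setswana No is 0.90 × 0.80 + 0.10 = 0.82.

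**4. What can be recovered afterwards.** Items 1 to 3 (any sex, number of male partners, number of female partners) identify abstinent patients, though a Setswana No at item 1 bypasses items 2 and 3. No other item on the form records the partner's HIV status or disclosure before the window.

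**The case against.** The strongest reply has four parts.

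- **Abstinence is identifiable.** Item 1 marks patients without recent sex, and an analysis plan could exclude them from items 10 and 11. This stands. It does not help for partners known to be HIV positive or told earlier.
- **Nobody is strictly forced.** The form is completed by an interviewer, has a result code for partial completion, and will be pre-tested. The English item 10 row carries no three-month limit of its own, so a recently abstinent patient might answer about an earlier occasion. This also stands, but a blank or an answer about another period is no more interpretable.
- **Many patients can answer.** Someone whose last partner was of unknown or negative status can answer English item 10. Someone who disclosed within the window, or never did, can answer item 11. This is correct. The fault affects identifiable groups only.
- **The consequence is limited.** Sexual behaviour is not in the between-arm objectives or the hypotheses. The counts of sex with and without condoms and of alcohol before sex are separate items with a zero option. This is correct too.

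A reader might go further and infer that earlier disclosure is scored as none, and that abstinent patients and those with HIV-positive partners are pushed into a risk answer, inflating risk from 14% to 44%. The documents do not support that. No scoring rule is given, the percentages are assumptions, and the risk direction fits only the English item 10. On the Setswana form the same No falls on the safe side.

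**Conclusion.** The point holds in limited form. Item 11, read literally, cannot separate earlier disclosure from none and can show a fall in a continuing couple when nothing has changed. Item 10 lacks an answer for patients without an applicable partner. It also appears to differ between languages in both direction and partner definition, so pooled answers are not interpretable as they stand. The two item 1 skips contradict each other.

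The size depends on rates that the protocol does not give, and the figures above are illustrations only. The finding on item 11 and the missing option rest on the English wording alone. The reversal of item 10 rests on my translation. The effect is confined to the sexual-behaviour parts of objectives 2 and 3; the AUDIT analysis, the adherence outcome and the sample size are untouched. It deserves correction because the lost information cannot be rebuilt later and the repair is cheap.

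**What to change.** Before the questionnaire pre-test and printing already in the time line:

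1. **Item 11, both languages.** Ask for a current state: *Does your last sex partner know your HIV status? Yes / No / No sex partner in the past 3 months.*
2. **Item 10, both languages.** Use the same direction and the same partner definition (unknown or negative status). Add *not applicable* for no sex in the past three months or no such partner. Analyse the item only among patients with such a partner. Have the Setswana wording checked against the English.
3. **Skip after item 1.** Use one identical rule: a No skips items 2 to 11, with the counts in items 2 to 9 coded 0 and items 10 and 11 coded not applicable.

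The cost is one reprinted page in each language. The one downside is a smaller denominator for item 10. Adding only a not-applicable box would not be enough, because the opposite directions in the two languages would remain.
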